### Participants and Research Eligibility

#### Preschools

Thirty preschools will be recruited into the trial. Preschools in Australia provide educational and developmental programs for children (3 to 5 years) for up to two years prior to the commencement of full-time primary school education [31]. Preschool services are usually provided by qualified teachers for approximately six hours per weekday [32]. Sixty-four percent of all 4-year-old children in New South Wales attend preschool, with an average attendance of 17 hours per week [33]. Each preschool in the study area provides, on average, care for 27 children per day [34].

A current list of all preschools in the region that are licensed to provide care for 3- to 5-year-old children will be obtained from the New South Wales Department of Community Services (the licensing agency). Preschools will be excluded from the trial if they provide meals to children in their care (as this limits parents' capacity to influence the foods their children consume), cater exclusively for children with special needs (given the specialist care required for such children), are Government preschools (as conduct of the research has not been approved by the New South Wales Government Department of Education and Training) or have participated in child healthy eating research projects within six months of the commencement of recruitment. Information regarding eligibility of preschool services will be confirmed by preschool supervisors during phone contact as part of the recruitment process.

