#### Primary outcome measure: fruit and vegetable consumption

The primary outcome is the change in the fruit and vegetable intake of the preschool children. Fruit and vegetable intake will be assessed using the fruit and vegetable subscale of the Children's Dietary Questionnaire. This questionnaire was developed to assess Australian children's dietary patterns in relation to current national guidelines and has been recommended for use in assessing the efficacy of interventions to improve children's eating habits [61].

This semi-quantitative food frequency questionnaire asks parents to report the frequency and variety of foods consumed by their children over the previous seven days and the previous 24 hours. Scores on the fruit and vegetable subscale range from 0 to 28, with a score of 14 recommended based on current national dietary guidelines [61]. A one-point increase on this subscale could equate to, for example, a child consuming on average an additional type of fruit or vegetable each day (variety), or consuming fruit or vegetables at an additional eating occasion each day (frequency). An increase of this magnitude of fruit and vegetable variety or frequency of consumption is consistent with effect sizes of fruit and vegetable consumption reported in previous child fruit and vegetable interventions, and has the potential to have significant public health impact [62]. Reliability and validity of this tool has been established using multiple samples of Australian children, including preschoolers [61]. The fruit and vegetable subscale was found to be internally consistent (∝ = 0.76), reliable (intra-class correlation coefficient = 0.75) and valid as assessed against a seven-day food checklist (Spearman's correlation coefficient = 0.58) [61].

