#### Sample size

A sample size of approximately 300 participants (150 per group) at the 18-month follow-up will allow a detectable difference between intervention and control groups of 1.27 on the fruit and vegetable subscale of the Children's Dietary Questionnaire, with 80% power at the 0.05 significance level. This sample size accounts for the effect of clustering by assuming an interclass correlation coefficient of 0.03 (unpublished data from the *Good for Kids *program) and assumes 10 participants per preschool remain at the 18-month follow-up (as explained below).

Four hundred participants will be required to be recruited at baseline to achieve the desired sample of 300 at the 18 month follow-up. Based on preschools caring for an average of 27 children each day [34], and assuming children attend preschool for an average of 2.8 days per week (i.e. 17 hours over 6-hour long days), it is expected that up to 48 parents of children, on average, will be eligible to participate in the trial from each consenting preschool. A parent participation rate of 30% [19] will yield approximately 14 parents per preschool at baseline, of whom 10 will remain at 18 months, assuming a 25% attrition rate [63]. It is thus estimated that 30 preschools will be required to generate a sample of 300 parents at the conclusion of the trial.

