#### Statistical analysis: primary outcome

All statistical analyses will be performed with SAS (version 9.2 or later) statistical software.

To assess the initial impact of the intervention and the extent to which any intervention effect is maintained in the longer term, the primary outcome analyses for the trial will be conducted on participant scores on the fruit and vegetable subscale of the Children's Dietary Questionnaire collected at the two-month and 18-month follow-up time periods. For the primary outcome analyses, an alpha value of 0.05 will be utilised to determine statistical significance.

Outcome data will be analysed using general estimating equations based on the intention-to-treat principle, where participants are analysed based on the groups to which they were allocated, regardless of the treatment type or exposure that they actually received [64]. General estimating equation models will account for any clustering effect of preschools. To ensure the results of the primary analysis are robust against the missing data assumption of the general estimating equation, a sensitivity analysis will be performed whereby participants' observations at baseline will be used as a substitute for subsequent missing data. A per-protocol analysis will also be conducted whereby outcome data will only be included in analyses if participants received and completed all four telephone support calls. Conducting both intention-to-treat and per-protocol analyses is recommended when assessing trial outcomes [64].

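### GEE with 30 preschools and no small-sample correction named: if the ordinary sandwich variance and a normal reference are used, the 5% test runs at about 7%

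*Protocol article*

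**What the plan says.** The protocol article, under Statistical analysis: primary outcome, makes GEE in SAS the primary method for the two-month and 18-month comparisons. On clustering it says "General estimating equation models will account for any clustering effect of preschools". On the test, "an alpha value of 0.05 will be utilised to determine statistical significance". It does not name the variance estimator, the working correlation, the reference distribution or any small-sample correction.

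The number of clusters is fixed under Participants and Research Eligibility: "Thirty preschools will be recruited into the trial". Allocation is 1:1, so about 15 per group.

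Under Sample size, the plan gives "A sample size of approximately 300 participants (150 per group) at the 18-month follow-up" and "a detectable difference between intervention and control groups of 1.27", "with 80% power at the 0.05 significance level", "assuming an interclass correlation coefficient of 0.03" and 10 parents per preschool still in the study. No standard deviation, formula or degrees of freedom are given.

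**The concern.** The robust (sandwich) variance of GEE is justified as the number of clusters grows. With 15 clusters per group it is biased downward, because each preschool's residual is measured from an arm mean that the preschool helped to set. Referring the statistic to the normal distribution then ignores the uncertainty of a variance estimated from about 28 independent pieces of information. Both errors act in the same direction: standard errors and critical values are too small.

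The assurance that GEE handles the clustering therefore holds for this design only with a correction that the text does not mention. At stake are p-values that are somewhat too small and intervals that are somewhat too narrow at both primary time points. The choice of variance could also decide a borderline result if it is made after the data are seen.

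**Working it through.** **Inputs from the protocol article.** 30 preschools, 15 per group; 10 parents per preschool at 18 months; 150 per group; ICC 0.03; alpha 0.05; difference 1.27; power 80%.

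**Assumptions.** Two-sided test (the sides are not stated); normally distributed outcome; the coefficient of variation (CV) of preschool size, which the article does not give, so a range is shown.

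**1. The plan's own figure.** Design effect = 1 + (10 − 1) × 0.03 = 1.27. Effective number per group = 150 / 1.27 = 118.1. The standard deviation is missing, so it has to be solved for:

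- normal approximation: SD = 1.27 / (2.802 × √(2/118.1)) = 1.27 / (2.802 × 0.1301) = 3.48
- t on 28 degrees of freedom: SD = 1.27 / (2.902 × 0.1301) = 3.36

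Either value reproduces 1.27 at 80% power. The document gives nothing that separates them.

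**2. Type I error, analytic approximation with equal sizes.** The reference distribution alone gives 2 × P(T28 > 1.96) = 6.0%. The uncorrected sandwich variance is on average 14/15 of its target, so the effective critical value is 1.96 × √(14/15) = 1.894, and 2 × P(T28 > 1.894) = 6.9%.

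**3. Type I error, simulation with no effect.** Exchangeable GEE, mean size 10, ICC 0.03. Simulation A used 6,000 runs per setting with the working correlation held at 0 or above. Simulation B used 20,000 runs per setting and let it go slightly negative.

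| Size CV | A: sandwich, z | A: Kauermann-Carroll, t28 | B: sandwich, z | B: Kauermann-Carroll, t28 | B: Mancl-DeRouen, t28 |
|---|---|---|---|---|---|
| 0 | 6.8% | 4.7% | 7.03% | 5.11% | 4.35% |
| 0.3 | 6.9% | 5.2% | 7.23% | 5.29% | 4.47% |
| 0.5 | 7.3% | 5.1% | not run | not run | not run |
| 0.6 | not run | not run | 8.28% | 6.02% | 4.88% |

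A further simulation with 20,000 runs per setting gave 7.0% to 7.3% for the ordinary sandwich with z, and about 5.2% with Kauermann-Carroll and t on 28. A GEE fit from a standard package with a baseline covariate (1,500 runs) gave 7.1%. The Monte Carlo standard error at 7% with 20,000 runs is √(0.07 × 0.93 / 20,000) = 0.18 percentage points.

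**4. Power, only if the plan used the normal approximation (SD 3.48).** The noncentral t on 28 degrees of freedom gives 77.2% for a difference of 1.27. The difference detectable with 80% power becomes 1.27 × 2.902 / 2.802 = 1.32. If the plan already used t on 28 (SD 3.36), power is 80% and nothing changes.

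**The case against.** The strongest reply is that the article contains no error. It never says that the standard errors are uncorrected. Its sentence on clustering is compatible with a bias-corrected variance and a t reference, and a journal article commonly leaves such detail to an analysis plan that is not shown. This stands as far as it goes: the 7% is conditional, and a reader who concluded that the trial will run a 7% test would be going beyond the text. It does not dispose of the point. The article fixes both the method and the small number of clusters, and it gives the assurance without qualification. The same section does take up another GEE assumption, the one on missing data, and sets a sensitivity analysis for it. Followed in its usual form, the plan gives an inflated test, and a better method is available at almost no cost.

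A reader might also infer that the 80% power ignores the cluster-level degrees of freedom. The documents do not support that. Without a standard deviation, the normal and the t calculation fit the stated figures equally well, and taking 2.802 as the starting multiplier presupposes the answer. Nor can it be shown that unequal preschool sizes were overlooked. Lower power figures on that account rest on an assumed CV, and the missing standard deviation prevents any check.

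Even under the normal approximation the loss is small: about 3 percentage points of power, or 0.05 points on a 0 to 28 scale. A baseline adjustment with correlation r would offset it when 1 − r² = (1.27/1.316)², that is, r of about 0.26. Testing at two time points is a separate matter and is not counted here.

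**Conclusion.** The point holds in conditional form. With 15 preschools per group, the ordinary sandwich variance with a normal reference turns a nominal 5% test into one of about 7%, a relative excess of about 40% (7/5 = 1.4). This rests on ICC 0.03, a mean of 10 parents per preschool and a size CV up to 0.5. At CV 0.6 one simulation reached 8.3%. The inflation is modest but applies to both primary time points.

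No fault in the power statement is established. The figures of 77% and 1.32 apply only if the calculation used a normal approximation.

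**What to change.** State in the analysis plan, before unblinded data are analysed, that both primary GEE analyses use one named bias-corrected sandwich variance (Kauermann-Carroll or Mancl-DeRouen) with a t reference on about 28 degrees of freedom. These are preschools minus cluster-level parameters, so 27 if the socio-economic stratum is in the model.

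The choice between the two matters a little. In simulation B, Mancl-DeRouen stayed below 5% even at size CV 0.6, where Kauermann-Carroll reached 6.0%. With equal sizes and SD 3.48, simulated power was 74.4% for Mancl-DeRouen and 76.6% for Kauermann-Carroll.

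Under Sample size, add the standard deviation and the formula. If the formula used a normal approximation, restate power as about 77% for 1.27, or the detectable difference as about 1.32, and say that this is before any gain from baseline adjustment. If it already used cluster degrees of freedom, say so and leave the figures alone.

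The cost is a few lines of text and a software setting, to be confirmed for the SAS procedure chosen. Intervals become slightly wider: with equal sizes and Kauermann-Carroll, by about 2.048 / 1.894 = 1.08, or 8%, where 2.048 is the 97.5% point of t on 28. No new data and no design change are needed.

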#### Intervention personnel, recruitment and training

Consistent with other telephone-based health behavioural interventions [20,21], intervention support will be delivered by trained telephone interviewers. Interviewers delivering the intervention will have experience in conducting health-related telephone surveys, but have no formal qualifications in psychology, dietetics, parenting, health promotion or other health professions. The use of telephone interviewers without specialist skills may mean that adoption of this intervention by government agencies is more feasible. Interviewers without specialist skills have previously been found to be effective in improving other health behaviours [20]. If effective in this context, their use may facilitate the adoption of this type of intervention where use of specialist staff may not be feasible due to cost and the shortage of staff with such skills.

To recruit suitable staff and to equip them with the necessary knowledge and skills to deliver the intervention, a pool of potential telephone interviewers was invited to attend a two-day training workshop. The training was developed and delivered by a registered dietitian, a clinical psychologist specialising in parenting, and health promotion practitioners (with post-graduate qualifications and experience in public health). The research team and clinical psychologist judged interviewer competency, based on the completion of role-plays [55] and small group exercises during training, and those considered sufficiently competent were selected to deliver the intervention. The selected interviewers were then required to complete a further minimum 10 hours of self-paced practice, including script and workbook familiarisation. They were also required to practise each script with a member of the research team to ensure that required levels of competency and adherence had been met [55] and that they were able to deliver the script in a confident, conversational style and respond appropriately to participant queries.

During the first two months of intervention delivery, all interviewers will participate in fortnightly group supervision, facilitated by a psychologist. A self-regulatory model of peer supervision [56] will be utilised to facilitate learning, improve interviewer performance and help standardise intervention delivery. Members of the research team will monitor the supervision sessions and provide feedback as required.

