#### Intervention monitoring

To ensure integrity of intervention delivery during the trial, members of the research team will have weekly contact with interviewers to keep abreast of common issues and concerns so that they may be addressed in a consistent manner. During each four-week batch of telephone calls, members of the research team will monitor at least two completed calls made by each interviewer to assess adherence with the intervention protocol. Specifically, the research team member will record whether the interviewer covers the key themes and information for each call, the extent to which the interviewer deviates from the script, the length of the call and whether the interviewer adequately answers any questions asked.

The records of the recruitment coordinator will be audited following the recruitment of each batch of participants. A separate member of the research team will review the dates on which allocation letters are mailed. They will also review the attempt dates, receipt dates and completion dates of intervention and data collection telephone calls for each trial participant. This periodic review of documentation will assess whether the intervention is progressing in a timely manner and in accordance with the study protocol [57].

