#### Process measures

The CATI system will record information regarding the outcome of each attempted call (e.g. engaged, answering machine, call-back arranged, call partially complete, call complete or refusal), the interviewer who attempted the call, the date and time of the attempt, the call duration and the responses provided by the participant throughout the call. During intervention delivery calls, participants will be asked whether they received the intervention resources and what homework activities they attempted. This will allow for an assessment of the extent to which the intervention was delivered and received as planned.

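### The primary model and sample size allow only for preschool clustering; if the interviewers who deliver the calls differ and work across preschools, the standard error will be somewhat too small

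*Protocol article*

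**What the plan says.** Under Statistical analysis: primary outcome, the article fixes the clustering structure in one sentence: "General estimating equation models will account for any clustering effect of preschools". It then lists two supplementary analyses, one replacing missing follow-up with the baseline value and one per protocol. Neither concerns interviewers.

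Under Sample size, the target is "A sample size of approximately 300 participants (150 per group) at the 18-month follow-up", inflated for a preschool ICC of 0.03 with 10 parents per preschool. No other correlation enters.

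The active treatment is four weekly scripted calls. On the staff, Intervention personnel, recruitment and training says: "Interviewers delivering the intervention will have experience in conducting health-related telephone surveys, but have no formal qualifications in psychology, dietetics, parenting, health promotion". They were chosen from a pool for judged competence, but the article does not say how many were chosen, how parents are assigned to them, or whether one interviewer makes all four calls to a parent. Controls are posted a booklet and have no delivery interviewer.

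The data to examine interviewers will exist. Process measures says that the call system records "the interviewer who attempted the call, the date and time of the attempt, the call duration", and Intervention monitoring has the team record, for monitored calls, "the extent to which the interviewer deviates from the script".

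**The concern.** Parents who share an interviewer may have correlated outcomes because they received the same person's version of the treatment. If an interviewer's parents come from several preschools, that correlation runs across the clusters in the model, and a preschool-level standard error does not see most of it. It is present in one arm only.

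At stake is the honesty of the confidence interval. Both Intervention personnel, recruitment and training and the Discussion look ahead to wider delivery by staff without specialist skills. That use concerns interviewers other than those employed in the trial, so variation between interviewers is part of the relevant uncertainty.

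**Working it through.** **The plan's own figures.**
- Design effect: 1 + (10 − 1) × 0.03 = 1.27.
- Recruitment: 300 / (1 − 0.25) = 400, as stated. Preschools: 30 × 10 = 300, as stated.
- The detectable difference ("will allow a detectable difference between intervention and control groups of 1.27 on the fruit and vegetable subscale", "with 80% power at the 0.05 significance level") cannot be reproduced because no standard deviation (SD) is given. Solved backwards with a two-sided normal approximation, SD = 1.27 / (2.8016 × √(2 × 1.27 / 150)) = 3.48. The standard-error ratios below do not depend on this SD.

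**Inputs.** From the article: 150 per arm at 18 months, 15 preschools per arm with 10 parents each, preschool ICC 0.03, and "an alpha value of 0.05 will be utilised to determine statistical significance" (taken as two-sided). Assumed, because the article does not give them: k interviewers with equal loads, interviewer ICC ρ, and each parent linked to one interviewer.

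**Interviewers fully crossed with preschools.** In units of SD²/150, the variance of the treatment difference is:
- true: 2 × 1.27 + (150/k − 1)ρ;
- seen by a preschool-only robust standard error: 2 × 1.27 + (9/k)ρ, since a few parents within a preschool share an interviewer by chance.

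The SE factor is √(true / seen), and the actual test size is 2 × P(Z > 1.96 / factor). For k = 8:

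| ρ | true | seen | SE factor | size of 5% test |
|---|---|---|---|---|
| 0.01 | 2.7175 | 2.5513 | 1.032 | 5.8% |
| 0.02 | 2.8950 | 2.5625 | 1.063 | 6.5% |
| 0.05 | 3.4275 | 2.5963 | 1.149 | 8.8% |

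Dropping the small (9/k)ρ term gives factors of 1.034, 1.068 and 1.162.

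**Simulation** (20,000 runs per setting; a t test on preschool means with 28 degrees of freedom standing in for the GEE). With ρ = 0 the size is 4.8 to 5.1%, as it should be. For k = 8 crossed, the empirical SE over the average reported SE is 0.1358/0.1302 = 1.04, 0.1391/0.1301 = 1.07 and 0.1503/0.1298 = 1.16, with sizes 6.0%, 6.4% and 8.7%. This agrees with the formula.

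**Sensitivity to the layout and number of interviewers** (size at ρ = 0.01 / 0.02 / 0.05):

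| Layout | Size of 5% test |
|---|---|
| 8 interviewers, whole preschools (simulation) | 5.5 / 5.7 / 6.7% |
| 15 interviewers, one per preschool (simulation) | 5.0 / 4.8 / 4.8% |
| 4 interviewers, crossed (formula) | 6.6 / 8.1 / 12.7% |
| 4 interviewers, whole preschools (simulation) | 6.5 / 7.4 / 11.0% |
| 15 interviewers, crossed (formula) | 5.4 / 5.8 / 6.9% |

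**Two-month analysis.** If all 200 per arm were still present (13.3 per preschool, design effect 1.37), k = 8 crossed gives SE factors of 1.040, 1.078 and 1.183, with sizes 5.9%, 6.9% and 9.7%.

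**Power.** With SD 3.48, k = 8 crossed and ρ = 0.02, the true SE is 3.48 × √(2.895/150) = 0.484. Power for a difference of 1.27 is then P(Z < 1.27/0.484 − 1.96), about 75% rather than 80%.

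**The case against.** A reader might infer that a small team delivers the calls and that the intervals therefore are too narrow. The documents do not support that as fact. No number of interviewers is given. The shortfall needs three things that are not stated: interviewers who differ in effect, a stable link between parent and interviewer, and interviewers who work across preschools.

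Several further points weigh against a strong claim:

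- Scripting, competence selection, at least ten hours of practice, group supervision and call monitoring are all there to reduce differences between interviewers. They show that differences were thought possible, but they also lower the likely ICC. A value of 0.05 would exceed the preschool ICC of 0.03.
- If the calls change nothing through any interviewer, interviewers cannot differ and this mechanism inflates nothing. The test sizes above apply when interviewer effects differ but average to zero. When the average effect is not zero, the same figures are the non-coverage of the 95% interval.
- The stated aim is efficacy. For inference about the interviewers actually employed, preschool-level error is defensible.
- The full analysis plan is not shown and may cover this.

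These points stand, and they limit both certainty and size. They do not remove the point. The article states a clustering structure and its supplementary analyses, and interviewers appear in neither. Staggered recruitment because of limited delivery capacity, four-week batches of calls and supervision of all interviewers as a group make it likely that the same people serve successive preschools, though that is an inference. Separate, blinded data-collection interviewers do not help, because the correlation arises in delivery.

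**Conclusion.** The point holds in conditional form. The model and the sample size allow for preschool clustering only, in a design where one arm has a second possible source of correlation. If interviewers differ and work across preschools, the reported standard error will be somewhat too small. For 8 interviewers and an interviewer ICC of 0.01 to 0.05, the true SE is about 3 to 16% larger than reported and the 5% test runs at about 6 to 9% when fully crossed. The test runs at about 5.5 to 6.7% when those interviewers serve whole preschools, and there is essentially no inflation with one interviewer per preschool. Fewer interviewers make it worse and more make it milder; calls shared among interviewers within a parent also weaken it. The number of interviewers, their ICC and the layout are assumptions throughout. The GEE at the unit of randomisation is not wrong, and nothing here calls for replacing it. This is a cheap improvement, not a fault that undermines the trial.

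**What to change.** Keep the GEE as the primary analysis. Add to Statistical analysis: primary outcome a pre-specified sensitivity analysis at two and 18 months: a partially nested linear mixed model with a preschool random effect in both arms and an interviewer random effect in the intervention arm only. Take the interviewer from the call-system record, either as the person who made most of a parent's calls or through multiple-membership weights, and state a rule for intervention parents with no completed call. Report the interviewer variance and the resulting interval beside the GEE result. State also how many interviewers delivered calls and how parents were assigned to them.

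Rostering need not change. Tying each parent to one named interviewer would strengthen the correlation at issue and alter delivery for an analytic purpose.

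The cost is one extra model on data already recorded. The downside is a slightly wider interval and, if interviewers are few, an imprecise estimate of their variance, which is why this belongs beside the primary result and not in its place.

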### Data Collection and Measures

Baseline and follow-up data will be collected through a CATI survey administered to all participants. The survey will take approximately 30 minutes to complete. Data collection interviewers will be provided with training to ensure that they understand and adhere to data collection protocols, and to practise the survey script.

Baseline data will be collected one to two weeks prior to intervention delivery. Calls will be monitored for adherence to the training protocol. Members of the research team will monitor approximately ten percent of the first batch of baseline calls and compare the delivery of the survey to the script as written. Any deviations from the protocol will be addressed with the interviewer immediately following the completion of the call. Each interviewer will then be monitored at least once in each subsequent batch of surveys to ensure consistency over time. The survey administered at baseline will be repeated at four time points: two, six, 12 and 18 months following baseline data collection. To minimise attrition, prior to follow-up data collection calls at six, 12 and 18 months, participants will receive letters thanking them for their participation to date and reminding them that they will shortly be telephoned to participate in follow-up phone calls [58].

Data collection interviewers will not participate in trial recruitment or intervention delivery and will be blind to participant group allocation. Furthermore, during each follow-up data collection interview, participants will be asked not to disclose their group allocation to the interviewers at the start of the telephone survey. To assess the effectiveness of the blinding, following the collection of trial outcome data, interviewers will be asked to nominate the groups to which they believe the participants were allocated [59].

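### Substituting baseline scores is a single fixed missing-data scenario, so it cannot show that the 18-month GEE result is robust, as the article says it will

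*Protocol article*

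**What the plan says.** The section on statistical analysis of the primary outcome plans a GEE analysis by intention to treat, with two and 18 months as the primary time points. It then states: "To ensure the results of the primary analysis are robust against the missing data assumption of the general estimating equation, a sensitivity analysis will be" carried out, in which each participant's "observations at baseline will be used as a substitute for subsequent missing data". The article names no other missing-data analysis. The per-protocol analysis that follows selects on exposure ("outcome data will only be included in analyses if participants received and completed all four telephone support calls") and does not address missing outcomes.

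The Sample size section plans for substantial loss: "Four hundred participants will be required to be recruited at baseline to achieve the desired sample of 300 at the 18 month follow-up", with about 14 parents per preschool at baseline "of whom 10 will remain at 18 months, assuming a 25% attrition rate". The section on data collection shows what would be available to inform a missing 18-month score: "The survey administered at baseline will be repeated at four time points: two, six, 12 and 18 months following baseline data collection".

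**The concern.** GEE fitted without weights to the available scores is in general valid only if missingness is completely at random given the covariates in the model. A useful sensitivity analysis would relax that assumption, or depart from it by stated amounts and show when the conclusion changes. Baseline substitution does neither. It adds one different and equally untestable assumption: every child without a later score stayed exactly at the baseline score, for up to 18 months, at an age of 3 to 5 years at entry.

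Two misreadings are at stake. A sound positive result could look weaker than it is because the estimate shrinks. A result biased by informative dropout could be reported as robust because the check returns much the same answer. The second matters more, because the article presents the check as its safeguard.

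**Working it through.** **Inputs from the article.** 400 parents recruited and 300 at 18 months; 25% attrition; 1:1 allocation; 30 preschools; ICC 0.03; 10 per preschool at 18 months; detectable difference "1.27 on the fruit and vegetable subscale of the Children's Dietary Questionnaire, with 80% power at the 0.05 significance level". A two-sided test is assumed.

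**Plan's own figure.** 300 / (1 - 0.25) = 400, which reproduces. So 0.25 x 400 = 100 participants would carry a baseline value at 18 months.

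**Implied SD.** None is stated. Design effect 1 + 9 x 0.03 = 1.27; effective n per arm 150 / 1.27 = 118.1; SD = 1.27 / [(1.96 + 0.84) x sqrt(2 / 118.1)] = 3.48. This is back-solved, not a figure from the article.

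**Expected difference under baseline substitution.** Let dI and dC be dropout in the intervention and control arms, c the mean control change and D the true difference. With dropout unrelated to outcome:

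(1 - dI)(c + D) - (1 - dC)c

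| dI, dC | c | D = 0 | D = 1.27 |
|---|---|---|---|
| 25%, 25% | any | 0 | 0.75 x 1.27 = 0.95 |
| 30%, 20% | +1 | 0.70 - 0.80 = -0.10 | 0.70 x 2.27 - 0.80 = 0.79 |
| 35%, 15% | +1 | 0.65 - 0.85 = -0.20 | 0.65 x 2.27 - 0.85 = 0.63 |
| 35%, 15% | -1 | -0.65 + 0.85 = +0.20 | 0.65 x 0.27 + 0.85 = 1.03 |

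The unequal splits and the drifts are assumptions. The sign of the bias depends on both, so the check is not reliably conservative.

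**Power under equal, non-informative 25% dropout, D = 1.27.** The answer depends on the form of the analysis.
- Follow-up scores without baseline adjustment: 400 / 30 = 13.3 per preschool; design effect 1 + 12.3 x 0.03 = 1.37; SE = 3.48 x sqrt(2 x 1.37 / 200) = 0.408; power = Phi(0.9525 / 0.408 - 1.96) = 65%, against 80% planned.
- Change scores, taking 3.48 as the SD of change: zero-change values also shrink the SD, to about 3.03, and the SE to 0.34-0.35, giving power of 77-79%.
- Simulation calibrated so that the observed-data analysis has 76-78% power (baseline/follow-up correlation 0.5 or 0.7): baseline substitution gives 77-78% for change scores, 73-75% with baseline adjustment and 66-68% for unadjusted scores.

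**Simulation under a true difference of zero.** 30 preschools of 13, SD 3.48, correlation 0.5, baseline-adjusted model, cluster-robust errors, 1,000 replicates. Each cell gives the mean estimate and rejection rate.

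| Dropout | Observed data | Baseline substitution |
|---|---|---|
| 25% each, c = +1 | 0.00 (6.7%) | 0.00 (6.6%) |
| 30% vs 20%, c = +1 | 0.00 (7.0%) | -0.11 (7.5%) |
| 35% vs 15%, c = -1 | 0.02 (5.8%) | 0.22 (12.3%) |
| 35% vs 15%, c = -2 | -0.01 (5.8%) | 0.40 (23.2%) |
| Informative, near 25% each, c = 0 | 0.60 (33%) | 0.57 (46%) |

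In the last row, intervention parents whose child changed least are more likely to leave. Both analyses are then wrong by about 0.6 points and agree with each other. The check rejects more often at nearly the same estimate, which reflects its smaller standard error.

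**The case against.** The strongest reply is that this is a supporting analysis, the primary GEE is untouched, and further sensitivity analyses usually belong in an analysis plan that is not shown. That limits the point to what the article fixes. But the article does more than stay silent: it chooses a method and states what the method achieves, and that statement is wrong whatever another document adds.

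Several stronger readings might be inferred, and the documents do not support them.
- *That the check loses a great deal of power.* The 65% figure needs unadjusted follow-up scores. The article defines the primary outcome as change, refers to scores in the analysis section, and does not say whether baseline is adjusted for. For change or baseline-adjusted analyses the loss is small.
- *That interim scores are discarded.* Only missing values are substituted. Observed 2-, 6- and 12-month scores stay in the data; they are just not used to fill a missing 18-month score.
- *That the check offers no protection.* It is one explicit departure scenario. With roughly equal, non-informative dropout it pulls the estimate towards zero, so an effect that survives it gives some reassurance.
- *That it will manufacture an effect.* This needs unequal dropout together with drift, and the article gives neither. In the milder case (30% against 20%, drift +1) the bias is 0.10 against the intervention and rejection barely moves. Retention letters go to participants without distinction of arm.
- *That a quarter of values are filled throughout.* The 25% applies at 18 months only.

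**Conclusion.** The point holds in a limited form. Baseline substitution is a single fixed scenario. It tests neither missing at random nor a range of departures, so it cannot support the article's claim of robustness.

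At 18 months it would set about 100 of 400 participants to zero change and shrink a true 1.27 to 0.95; this follows from the article's own 25% if dropout is equal and non-informative. The biases of -0.10 to +0.20 under a true difference of zero, and the informative-dropout result (0.60 and 0.57), show what can happen. They rest on assumed dropout splits, drift, correlation and dropout mechanism, and on the back-solved SD, and they do not predict this trial.

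Nothing here shows that the primary analysis is wrong. The check should be changed because it is the only missing-data safeguard the article names for a primary time point with a planned loss of one quarter.

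**What to change.** Make the main missing-data sensitivity analysis multiple imputation under missing at random, done separately by arm. Use the baseline score and all observed 2-, 6-, 12- and 18-month scores, allow for preschool, and follow it with the same GEE. Add a delta-adjusted version that shifts the imputed scores separately in each arm, and report the shifts at which the conclusion changes.

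Baseline substitution may be kept as one scenario, labelled as assuming no change from baseline in those with missing scores. Remove the statement that it ensures robustness.

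The cost is revised wording and modest extra programming. No new data are needed, because the interim surveys are already planned.
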